## 5. TREATMENT OF SUBJECTS

### 5.1. Investigational product/treatment

After the vascular anastomosis the transplant surgeon will perform an extravesical anastomosis as described by Lich-Gregoir (9, 10). A myotomy of 2-3 cm on the anterolateral surface of the bladder dome is performed to expose the mucosa of the bladder wall. A small incision is made in the mucosa. The transplanted ureter is trimmed and spatulated posteriorly. The bladder mucosa is sutured to the ureter with a running absorbable suture. The detrusor muscle is closed over the anastomosis by one or two interrupted absorbable sutures to create a sub-mucosal tunnel with an antireflux mechanism. Participants who are randomized to external stenting will receive an externalised 7 French ureteric stent (Teleflex®). Participants who are randomized to double J stenting will receive a short (12cm) internal Double J 7 French stent(Teleflex®). The tip of both stents will be positioned in the pelvis of the transplanted kidney. The position of the stent will be verified during ultrasonography, which is being performed the day after surgery as standard post-operative care. External stents will be removed 9 days post-operatively. Double J stents will be removed after 3 weeks by cystoscopy in the outpatient clinic of the department of urology. An antibiotic prophylaxis will be used during this procedure based on the latest urinary cultures.

### 5.2. Use of co-intervention (if applicable)

Recipients will be asked to fill in questionnaires at different time point after transplantation, including a Visual Analogue Score (VAS), quality of life questionnaire (SF-36), Euro-QoL (EQ-5D) and 'Werk en Zorg' questionnaires.

### 5.3. Escape medication (if applicable)

Not applicable

## **6. INVESTIGATIONAL PRODUCT**

### **6.1. Name and description of investigational product(s)**

Single J stent (Teleflex) 7fr

Short (12cm) double J stent (Teleflex) 7fr

Both stents are CE approved and widely used worldwide

### **6.2. Summary of findings from non-clinical studies**

See brochure of Teleflex

### **6.3. Summary of findings from clinical studies**

Not applicable

### **6.4. Summary of known and potential risks and benefits**

Not applicable

### **6.5. Description and justification of route of administration and dosage**

Not applicable

### **6.6. Dosages, dosage modifications and method of administration**

Not applicable

### **6.7. Preparation and labelling of Investigational Medicinal Product**

Not applicable

### **6.8. Drug accountability**

Not applicable

## **7. NON-INVESTIGATIONAL PRODUCT**

This section is not applicable for this study and is therefore left blank.

**7.1. Name and description of non-investigational product(s)**

**7.2. Summary of findings from non-clinical studies**

**7.3. Summary of findings from clinical studies**

**7.4. Summary of known and potential risks and benefits**

**7.5. Description and justification of route of administration and dosage**

**7.6. Dosages, dosage modifications and method of administration**

**7.7. Preparation and labelling of Non Investigational Medicinal Product**

**7.8. Drug accountability**

## **8. METHODS**

### **8.1. Study parameters/endpoints**

#### **8.1.1. Main study parameter/endpoint**

Percutaneous nephrostomy (PCN) drainages.

#### **8.1.2. Secondary study parameters/endpoints (if applicable)**

Urinary tract infection

Haematuria

Radiological interventions

Surgical re-interventions

Stent obstruction or dysfunction

Additionally, a quality of life and cost effectiveness analysis will be performed by using questionnaires. Validated questionnaires for pain, quality of life, health state, work efforts and disabilities in daily life are measured by the VAS, Euro-QoL, SF-36 and 'Werk en Zorg'.

#### **8.1.3. Other study parameters (if applicable)**

Other study parameters are baseline values, which might intervene with the main study parameter: donor age and gender, recipient age and gender, body mass index, smoking, ASA classification, operation time and return to normal daily activities.

### **8.2. Randomisation, blinding and treatment allocation**

This will be a single-centre randomized controlled trial. Randomization will be performed after intubation in the operation room by an electronic system, stratified for type of donor (living/ deceased). Since patients and physicians will notice post operatively the presence of an externalized stent, the study cannot be blinded.

### **8.3. Study procedures**

The work-up for kidney transplantation will be according to the standard protocol. Our "intervention" is internal Double J stenting, since externalized stenting is now standard practice during kidney transplantation.

Post operatively, the double J stent group will have an additional cystoscopy after 3 weeks to remove the stent. Recipients will be asked to fill out a Visual Analogue Score

(VAS), quality of life questionnaire (SF-36), the Euro-Qol (EQ-5D) and the 'Werk en Zorg' at different times (Table 1).

Table 1.

| Time point    | VAS | Euro-Qol | SF-36 | Werk en Zorg |
|---------------|-----|----------|-------|--------------|
| Pre-operative | X   | X        | X     | X            |
| Week 2        | X   | X        | X     | X            |
| Week 6        | X   | X        | X     | X            |
| Month 6       | X   | X        | X     | X            |

- VAS = Visual Analogue Score. Scores the amount of pain and nausea on a scale from none to severe on the basis of numbers (i.e. 0-10).
- EuroQol: Scores the ability to perform daily tasks and measures health outcome.
- SF-36: Scores pain, ability to perform daily tasks and the quality of life.
- Work related questionnaires: score the ability to perform daily tasks.

#### 8.4. Withdrawal of individual subjects

Subjects can leave the study at any time for any reason if they wish to do so without any consequences. The investigator can decide to withdraw a subject from the study for urgent medical reasons.

##### 8.4.1. Specific criteria for withdrawal (if applicable)

Not applicable

#### 8.5. Replacement of individual subjects after withdrawal

Patients will be randomized after intubation, so therefore they will receive the treatment as determined by randomisation. Participants can decide to not fill in the questionnaires anymore. These patients will not be replaced, as we have anticipated on some missing data in our power calculation.

#### 8.6. Follow-up of subjects withdrawn from treatment

Subjects will not be followed up after the study withdrawal, as there are no long term side effects expected. Only patients who insisted to withdrawn from the study who received an internal Double J stent, prior to the removal on 3 weeks after transplantation, will be

stimulated to still have this stent removed after 3 weeks. Prolonged internal stent insertion (> 3 months) has been correlated with stone formations and infections (11) .

#### **8.7. Premature termination of the study**

If safety issues arise (according to the DSMB) the study may be ended prematurely

## 9. SAFETY REPORTING

### 9.1. Temporary halt for reasons of subject safety

In accordance to section 10, subsection 4, of the WMO, the sponsor will suspend the study if there is sufficient ground that continuation of the study will jeopardise subject health or safety. The sponsor will notify the accredited METC without undue delay of a temporary halt including the reason for such an action. The study will be suspended pending a further positive decision by the accredited METC. The investigator will take care that all subjects are kept informed.

### 9.2. AEs, SAEs and SUSARs

#### 9.2.1. Adverse events (AEs)

Adverse events are defined as any undesirable experience occurring to a subject during the study, whether or not considered related to [the investigational product / trial procedure/ the experimental intervention]. All adverse events reported spontaneously by the subject or observed by the investigator or his staff will be recorded.

#### 9.2.2. Serious adverse events (SAEs)

A serious adverse event is any untoward medical occurrence or effect that

- results in death;
- is life threatening (at the time of the event);
- requires hospitalisation or prolongation of existing inpatients' hospitalisation;
- requires surgical intervention
- requires PCN placement
- results in persistent or significant disability or incapacity;
- is a congenital anomaly or birth defect; or
- any other important medical event that did not result in any of the outcomes listed above due to medical or surgical intervention but could have been based upon appropriate judgement by the investigator.

An elective hospital admission will not be considered as a serious adverse event.

The investigator will report all SAEs to the sponsor without undue delay after obtaining knowledge of the events, except for the following SAEs: readmissions,

surgical interventions and PCN placements. These events will be reported once a month.

The sponsor will report the SAEs through the web portal *ToetsingOnline* to the accredited METC that approved the protocol, within 7 days of first knowledge for SAEs that result in death or are life threatening followed by a period of maximum of 8 days to complete the initial preliminary report. All other SAEs will be reported within a period of maximum 15 days after the sponsor has first knowledge of the serious adverse events.

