### **9.5. [Data Safety Monitoring Board (DSMB) / Safety Committee]**

A Data Safety Monitoring Board will be installed to evaluate this study after every 50 included patients. The following people will take place in this Board:

[name]. [name], department of gastroenterology and hepatology

[name], department of biostatistics

[name], department of surgery

The advice(s) of the DSMB will only be sent to the sponsor of the study. Should the sponsor decide not to fully implement the advice of the DSMB, the sponsor will send the advice to the reviewing METC, including a note to substantiate why (part of) the advice of the DSMB will not be followed.

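### Monthly reporting of readmissions, surgical interventions and PCN placements makes no exception for those that are life-threatening

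*Protocol*

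**What the plan says.** Protocol section 9.2.2 lists the criteria that make an event serious. Death, threat to life ("is life threatening (at the time of the event"), hospitalisation or its prolongation, surgical intervention and PCN placement are separate entries. The only exclusion stated there is: "An elective hospital admission will not be considered as a serious adverse event".

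Reporting then runs in two steps.

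- **Investigator to sponsor.** The default is "The investigator will report all SAEs to the sponsor without undue delay after obtaining knowledge of the events". It is qualified by "except for the following SAEs: readmissions", followed by "surgical interventions and PCN placements. These events will be reported once a month".
- **Sponsor to METC.** The sponsor reports "within 7 days of first knowledge for SAEs that result in death or are life threatening". For the rest: "All other SAEs will be reported within a period of maximum 15 days after the sponsor has first knowledge".

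Section 9.5 adds: "A Data Safety Monitoring Board will be installed to evaluate this study after every 50 included patients".

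**The concern.** The exemption from prompt reporting names three kinds of event and attaches no condition about how dangerous the event was. Yet threat to life is its own criterion in the same list, and one event can meet several criteria: an emergency reoperation or an acute readmission may well be life-threatening. The protocol wants such events before the METC within a week, but that clock starts only when the sponsor knows. If the first step can take a month, the second step's short deadline protects little.

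The exempted categories are also central to the stent comparison. PCN placement is the primary endpoint (sections 8.1.1 and 10.1), and surgical re-interventions are a secondary endpoint (section 8.1.2). Section 9.1 obliges the sponsor to suspend the study when there are grounds to think subjects are at risk, and the sponsor can act only on what it has been told.

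**Working it through.** No figure in the plan needs reproducing. The check sets the rules side by side and adds up the stated intervals.

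**Step 1: which route does each kind of SAE take under 9.2.2?**

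| Event | Investigator to sponsor | Sponsor to METC |
|---|---|---|
| Not one of the three types, life-threatening | prompt | 7 days from first knowledge |
| One of the three types, not life-threatening | monthly | 15 days from the sponsor's first knowledge |
| One of the three types and life-threatening | not settled; monthly if read literally | 7 days from first knowledge |
| Death | prompt, as a separate criterion that is not exempted | 7 days from first knowledge |

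The third row is the problem.

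**Step 2: does another section supply a faster route for that row?**

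- 9.1 (temporary halt) sets no reporting time.
- 9.2.3 declares SUSAR reporting not applicable.
- 9.3 is an annual report.
- 9.4 concerns follow-up of events already recorded.
- 9.5 has the DSMB evaluate per 50 patients. At the 100 recipients per year in section 3, that is 50 / 100 = 0.5 year, or about every six months.

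None does.

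**Step 3: how long can it take?** Let D be the days from the investigator's knowledge to the sponsor's. The METC is told by day D + 7 at the latest. A month is taken as up to 31 days.

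- Default route, D close to 0: about 0 + 7 = 7 days.
- Monthly route, worst case, D = 31: 31 + 7 = 38 days.
- Monthly route, average, assuming events fall evenly over the month, D = 31 / 2 = 15.5: 15.5 + 7 = 22.5 days.
- Sponsor and investigator effectively the same party, D = 0: 7 days, with no loss.

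The result therefore ranges from no added delay to about 31 added days, depending on when in the month the event occurs and on how separate the two roles are.

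**The case against.** The strongest reply is that the exemption can be read more narrowly. Its three categories match three entries in the list of criteria (hospitalisation, surgery, PCN), while death and threat to life are not among those exempted. On that reading, an event that also meets a non-exempted criterion stays on the prompt route, and the separate 7-day track fits this. The reading is reasonable and may be what was intended. It is not written down, however, and a site applying the sentence as it stands could batch such an event without breaking any rule.

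Several stronger conclusions that a reader might draw are not supported:

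- **That the two rules contradict each other, or that the 7-day rule is breached.** They govern different steps and can both be followed. The start of the clock moves, and the deadline itself is kept.
- **That fatal events are batched.** Death is its own criterion and is not exempted, so a death after reoperation is reportable promptly even if the reoperation itself is listed later.
- **That a month is the usual delay.** It is the maximum. The trial has one centre, and sections 12.4 and 12.5 write sponsor and investigator as alternatives, so the roles may overlap. Section 9.2.2 nevertheless treats them as sender and receiver.
- **That the DSMB works from stale data.** Section 9.5 does not say that the board relies on the monthly list, and with reviews about six months apart a lag of up to a month would matter little.
- **That the patients randomised meanwhile measure the harm.** Planned accrual is 100 / 12 = 8.3 per month, but no section makes a single such event a trigger for a halt.

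Batching expected endpoint events is itself a proportionate choice for two CE-approved stents, and it is not in dispute. What remains is the life-threatening subset.

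**Conclusion.** The point holds in limited form. Section 9.2.2 exempts three event types from prompt reporting without regard to threat to life, and no other section closes the gap. Followed literally, it lets a non-fatal, life-threatening event of these types reach the sponsor up to about 31 days, and the METC up to about 38 days, after the investigator knew of it. These figures assume a 31-day month, separate sponsor and investigator, and the literal reading of the exemption; if the last two do not hold, the added delay shrinks or disappears. This is a weakness in safety reporting that should be corrected. It has no bearing on the sample size, the primary analysis or the validity of the comparison.

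**What to change.** Reconcile the two rules in 9.2.2 with one clause. Monthly reporting would apply only to readmissions, surgical interventions and PCN placements that are neither fatal nor life-threatening; any SAE meeting either of those criteria would go to the sponsor on the prompt default route. Naming fatal events as well removes doubt about a reoperation or readmission that ends in death. If the narrower reading was always meant, the clause merely records it. The cost is a short protocol amendment and a handful of extra individual reports. Monthly batching of routine endpoint events stays as it is, and no change to the DSMB arrangements is needed for this point.

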#### **9.2.3. Suspected unexpected serious adverse reactions (SUSARs)**

Not applicable for this study due to the lack of an investigational medicinal product.

### **9.3. Annual safety report**

In addition to the expedited reporting of SAEs, the sponsor will submit, once a year throughout the clinical trial, a safety report to the accredited METC, competent authority, and competent authorities of the concerned Member States.

This safety report consists of:

- a list of all suspected (unexpected or expected) serious adverse reactions, along with an aggregated summary table of all reported serious adverse reactions, ordered by organ system, per study;
- a report concerning the safety of the subjects, consisting of a complete safety analysis and an evaluation of the balance between the efficacy and the harmfulness of the medicine under investigation.

### **9.4. Follow-up of adverse events**

All AEs will be followed until they have abated, or until a stable situation has been reached. Depending on the event, follow up may require additional tests or medical procedures as indicated, and/or referral to the general physician or a medical specialist. SAEs need to be reported till end of study within the Netherlands, as defined in the protocol

### **9.5. [Data Safety Monitoring Board (DSMB) / Safety Committee]**

A Data Safety Monitoring Board will be installed to evaluate this study after every 50 included patients. The following people will take place in this Board:

[name]. [name], department of gastroenterology and hepatology

[name], department of biostatistics

[name], department of surgery

The advice(s) of the DSMB will only be sent to the sponsor of the study. Should the sponsor decide not to fully implement the advice of the DSMB, the sponsor will send the advice to the reviewing METC, including a note to substantiate why (part of) the advice of the DSMB will not be followed.

## 10. STATISTICAL ANALYSIS

### 10.1. Primary study parameter(s)

The primary study parameter is PCN placement within six months after transplantation. We will present this outcome in both arms both as a number and as a percentage. We will test if the probability of PCN placement is equal by means of Fisher's Exact test. A p-value below 0.05 (two sided) will be considered as statistically significant. All patients will be analyzed by the intention-to-treat approach.

### 10.2. Secondary study parameter(s)

The following outcomes will be studied using a linear mixed model:

- The level of creatinin and eGFR after transplantation
- The answers to the SF-36 questionnaire
- The answers to the EuroQol questionnaire
- The answers to the work related questionnaire

As predictors we use indicator variables for the different time points and an interaction of each of the follow-up time points with the treatment arm. Note that at baseline we see both arms of the trial as a single group.

For each response we choose the most suitable covariance structure from the compound Symmetry, compound symmetry heteroskedastic autoregressive, autoregressive Heteroskedastic, Toeplitz and heteroskedastic Toeplitz based on the Akaike information criteria. Nonsignificant terms will not be removed from the model. The primary contrast we test is whether the profiles of the arms overlap. When the result of this multivariate test is significant we will also test the results at the various follow-up time points. Note that we will not apply a correction for multiple testing looking at multiple responses.

The following categorical outcomes will be compared between the treatment arms by means of a continuity corrected Chi square test:

- Hematuria
- Urinary tract infection
- Urosepsis
- Reoperation
- Radiologic interventions
- Tacrolimus toxicity
- Kidney replacement therapy
- Rejection
- Graft failure
- 

When any cell is empty or when more than 20% of the expected counts are less than five Fishers exact test will be performed for this outcome instead of the Chi square test.

The following continuous outcomes will be compared between the treatment arms by means of a Mann-Whitney U test:

- First and second warm ischemia time
- Cold ischemia time
- Time needed to make an urether-bladder anastomosis
- Blood loss during transplantation
- Duration of transplantation
- Duration of admission

All tests will be performed in a two-sided fashion with an alpha of 0.05. No multiplicity adjustment will be made. We will present the baseline characteristics of both treatment arms by showing the median and IQR for continuous variables and numbers and percentages for categorical variables. No statistical test will be performed on these values.

The cost effectiveness of the double J stent will be calculated as followed:

$$\frac{\text{Costs Double J stent} - \text{Costs Splint}}{\text{Percentage of PCN placements in Double J stent arm} - \text{Percentage of PCN placements in Splint arm}}$$

The costs of the double J stent will include the costs of the cystoscopy in the outpatient clinic for the removal of the double J stent.

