### **10.3. Other study parameters**

Not applicable

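### The creatinine and eGFR mixed models in section 10.2 omit donor type, the stratification factor, and the donor and recipient ages already collected: valid, but less precise than it could be

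*Protocol*

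**What the plan says.** Section 10.2 puts creatinine, eGFR and three sets of questionnaire answers into linear mixed models with one shared predictor list: "As predictors we use indicator variables for the different time points and an interaction of each of the follow-up time points" with arm. Baseline is handled by a common mean: "Note that at baseline we see both arms of the trial as a single group". The list is closed in one direction, since "Nonsignificant terms will not be removed from the model", and no rule brings a covariate in.

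The graft-function outcomes are defined as "The level of creatinin and eGFR after transplantation". The questionnaires, by contrast, have a pre-operative assessment (section 8.3, Table 1).

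Section 8.1.3 lists further variables: "donor age and gender, recipient age and gender, body mass index, smoking, ASA classification, operation time and return to normal daily activities". Section 8.2 stratifies randomisation by living or deceased donor. Section 10.3, on other study parameters, reads "Not applicable". Section 10.2 does plan a descriptive summary of baseline characteristics by arm, without tests.

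**The concern.** In a linear model, a prognostic variable fixed before randomisation removes between-patient variance from the error term at almost no cost. For the questionnaires, the patient's own pre-operative score already does much of this through the common-baseline model. For creatinine and eGFR it cannot, because any value taken before surgery describes the recipient's failing kidneys and not the graft. Donor type and the donor's and recipient's ages are natural substitutes. All are known before randomisation, and none is in the model.

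Donor type raises a second matter. Stratification tends to balance it between arms, so the true sampling variability of the arm difference no longer contains the donor-type component. A model without donor type still counts that component as residual variance, and so reports a standard error larger than the design warrants.

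At stake is the width of the intervals for the graft-function comparison.

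**Working it through.** **The plan's own figure.** The only sample-size figure is 149 per arm for 80% power with Fisher's exact test, 9% against 1.5%, two-sided alpha 0.05 (section 4.4). Exact enumeration gives 79.8% power at 149 and 80.2% at 150 per arm, so the figure reproduces. It concerns the primary endpoint; the protocol gives no precision or power figure for the mixed models.

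**Inputs.** From the protocol: 150 per arm, 300 in total (4.4), and two-sided alpha 0.05 (10.2). Assumed: R², the share of between-patient variance at one time point that the added covariates explain.

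**Gain.** The standard error of the arm contrast is multiplied by √(1 − R²), and the equivalent total sample is 300/(1 − R²). Without covariates, the difference detectable with 80% power at one time point is (1.960 + 0.842) × √(2/150) = 0.323 SD. The last column gives the power at that same difference after adjustment.

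| Assumed R² | SE factor | SE reduction | Equivalent total N | Power at 0.323 SD |
|---|---|---|---|---|
| 2% | 0.990 | 1.0% | 306 | 80.8% |
| 5% | 0.975 | 2.5% | 316 | 82.0% |
| 10% | 0.949 | 5.1% | 333 | 84.0% |
| 20% | 0.894 | 10.6% | 375 | 87.9% |
| 30% | 0.837 | 16.3% | 429 | 91.8% |

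The power column is a single-time-point approximation. Section 10.2 first tests whether the arm profiles overlap, and power for that test was not computed.

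**Cost.** Fitting k covariates inflates the standard error by about √(298/(298 − k)): 0.3% for k = 2, 0.5% for k = 3 (√(298/295) = 1.005), 0.8% for k = 5 and 1.4% for k = 8. At R² = 2%, three covariates still give a small net gain (0.990 × 1.005 = 0.995), while eight give a trivial loss (0.990 × 1.014 = 1.004). A short list is therefore preferable.

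**Why the baseline device does not fill the gap.** If the baseline value has correlation ρ with the follow-up value, the common-baseline model multiplies the standard error by about √(1 − ρ²). For an assumed ρ of 0.5, plausible for a questionnaire score, the factor is 0.866. For an assumed ρ of 0 or 0.1, as might hold for a recipient's own pre-transplant creatinine, it is 1.000 or 0.995.

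**Stratification factor.** Assume exact balance of donor type between arms and let donor type alone explain R². The true variance of the contrast is then (1 − R²) times the variance the model reports, and a nominal 5% test rejects only when |Z| exceeds 1.96/√(1 − R²):

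- R² = 5%: threshold 2.011, actual level about 4.4%
- R² = 10%: threshold 2.066, actual level about 3.9%
- R² = 20%: threshold 2.191, actual level about 2.8%

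The distortion is conservative.

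**The case against.** The strongest reply is that nothing here is wrong. A constrained longitudinal model with time and arm-by-time terms is prespecified and valid, and unbiased under randomisation. A richer covariate set is a preference, and often one for a SAP. Creatinine and eGFR also rank low: they are absent from the objectives (section 2) and from the secondary endpoint list (8.1.2), and the trial was not sized for them. Most of this stands, and it is why the point is framed as an improvement. It does not dispose of the point, because section 10.2 names the predictors, and a SAP that followed it as written would omit even the stratification factor.

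Several stronger readings are tempting, and the protocol does not support them:

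- **Chance imbalance in donor age corrupts the arm estimate.** It does not bias it. The unadjusted standard error already allows for chance imbalance.
- **Sections 8.1.3 and 10.3 collect variables and then discard them.** Section 8.1.3 ties them to the main study parameter, which is PCN placement, and not to graft function. Section 10.2 also summarises baseline characteristics by arm, so the entry in 10.3 is not a contradiction.
- **The 8.1.3 variables are the only source of precision.** Donor type is not on that list and is arguably the best-supported candidate. Repeated measurements also contribute.
- **The questionnaire models need the same covariates.** They already use the pre-operative score, and no further gain has been shown.

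The objection that R² is assumed throughout also stands. Near 2% the benefit is negligible.

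**Conclusion.** The point holds as an efficiency weakness confined to creatinine and eGFR. The planned estimates are unbiased and their tests valid. They are less precise than the available data allow, and they are conservative to the extent that donor type is prognostic and balanced by the stratification. The reduction in standard error runs from about 1% to about 16% for an assumed R² of 2% to 30%, against 1% or less for up to five added terms. The protocol gives no figure that would place R² within that range. A reader might infer that the graft-function comparison is biased or that the primary result is affected. Neither follows, since the primary Fisher test is untouched.

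**What to change.** In section 10.2, state that the creatinine and eGFR models include donor type (living or deceased), donor age and recipient age as fixed effects, with time interactions for donor type and donor age if wanted. Name them before any outcome data are seen, so that the choice cannot look data-driven. Restrict adjustment to values fixed before randomisation. This rules out two items on the 8.1.3 list, the duration of surgery and the resumption of daily activities, which arise after randomisation although listed there as baseline values. Leave the questionnaire models and the primary analysis as they are.

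The cost is a wording change in the protocol or SAP. Donor and recipient ages are already collected and donor type is needed for randomisation, so no new data are required. Three main effects cost about 0.5% of the standard error; the optional time interactions add a little more.

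### The common-baseline mixed model in Protocol section 10.2 is applied to creatinine and eGFR without exception, although these graft markers have no stated baseline; they are better modelled on post-transplant values only.

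*Protocol*

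**What the plan says.** Section 10.2 lists four groups of responses for one linear mixed model: creatinine and eGFR, SF-36, EuroQol and the work questionnaire. The graft markers are described as "The level of creatinin and eGFR after transplantation". The fixed effects are the same for all: "As predictors we use indicator variables for the different time points and an interaction of each of the follow-up time points with the treatment arm". Then comes "Note that at baseline we see both arms of the trial as a single group", with no exception for creatinine and eGFR.

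The covariance structure is chosen by AIC from compound symmetry, autoregressive and Toeplitz forms and heteroskedastic versions of them (the list ends "autoregressive Heteroskedastic, Toeplitz and heteroskedastic Toeplitz based on the Akaike information criteria"). No unstructured option is listed. The test is joint: "The primary contrast we test is whether the profiles of the arms overlap". Single time points are tested only if it is significant.

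Table 1 in section 8.3 has the row "Pre-operative | X | X | X | X", and its columns are VAS, Euro-Qol, SF-36 and Werk en Zorg. Creatinine and eGFR are not in that table. Section 8.2 places randomisation after intubation, so any pre-operative value precedes it.

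**The concern.** A common baseline mean is a sound device when every patient has a pre-randomisation measurement of the same quantity. The questionnaires meet that condition. For creatinine and eGFR, the quantity of interest is the function of the graft, which does not exist in the recipient before the operation. A pre-operative value measures the native kidneys of patients whom section 1 describes as having chronic kidney failure, so there is little reason to expect it to predict graft function well.

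The stated model therefore leaves open which value, if any, plays the part of baseline, and the consequences differ by choice. At stake is the precision and error rate of the kidney-function comparison between two drainage devices. This is a secondary analysis with no multiplicity adjustment.

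**Working it through.** **The plan's own figure.** Section 10.2 gives no number for this model. The one figure that can be checked is the sample size in section 4.4: 9% against 1.5%, two-sided 0.05, Fisher's exact test, 149 patients (read as per arm). Exact enumeration gives power 0.798 at 149 and 0.802 at 150 per arm, so it reproduces. Nothing below changes it.

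**Common formula.** With complete data, the constrained model estimates the effect at follow-up t as

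D_t − b × D_0, with b = cov(t,0)/var(0),

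where D is the observed difference between arms. The protocol gives no correlations or SDs, so those below are assumptions.

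**Case 1: pre-operative value as baseline.** Randomisation makes the expected D_0 zero, so there is no bias. Take one baseline and three follow-ups, true correlation r0 of baseline with each follow-up, and ρ among follow-ups. Heteroskedastic compound symmetry frees the SDs but allows a single correlation c. Its average value is c = (3r0 + 3ρ)/6 = (r0 + ρ)/2. On the standardised scale:

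- actual variance = 1 − 2c·r0 + c²
- variance the model reports = 1 − c²
- actual type I error = 2 × [1 − Φ(1.96 × √(reported/actual))]

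| r0 | ρ | c | Actual | Reported | Type I error |
|---|---|---|---|---|---|
| 0 | 0.5 | 0.25 | 1.0625 | 0.9375 | 0.066 |
| 0 | 0.7 | 0.35 | 1.1225 | 0.8775 | 0.083 |
| 0.2 | 0.5 | 0.35 | 0.9825 | 0.8775 | 0.064 |
| 0.2 | 0.7 | 0.45 | 1.0225 | 0.7975 | 0.083 |

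This is about 0.06 to 0.08 per time point. The averaging is an approximation. Letting the likelihood also settle the SDs gives 0.068 to 0.096 per time point and 0.060 to 0.084 for the joint test. Across all the heteroskedastic structures the per-time-point range is about 0.05 to 0.11.

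On precision, the best possible gain from such a baseline is r0², that is 0 to 4% of the variance. With the weight that compound symmetry imposes, the actual variance is 0.98 to 1.12 times the unadjusted one: between 2% saved and 12% lost.

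**Case 2: only post-transplant values entered.** Every time point is then a follow-up with its own arm term. There is no baseline row, and the constraint acts on nothing.

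**Case 3: a post-operative value taken as baseline.** The text does not say this. If it were done, the expected estimate would be δ_later − ρ × (SD ratio) × δ_first. With equal SDs and the full effect already present at the first value, the share kept is 1 − ρ: 70%, 50% and 30% at ρ = 0.3, 0.5 and 0.7. With half the effect present early it is 1 − ρ/2: 85%, 75% and 65%. With no early effect nothing is lost.

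For scale, take 150 per arm, three follow-ups, an effect of 0.33 SD and ρ = 0.5:

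- Follow-ups only: noncentrality 0.33² × 75 × 3/(1 + 2 × 0.5) = 12.25 on 3 df, power 0.85.
- Constrained, full early effect: 0.165² × 75 × 3/(0.75 + 2 × 0.25) = 4.90 on 3 df, power 0.43.

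**Donor covariates.** A covariate correlated r with the outcome removes r² of the variance, equivalent to 1/(1 − r²) times the patients. For an assumed r of 0.3 to 0.5: r² = 0.09 to 0.25, and 1/(1 − r²) = 1.10 to 1.33.

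**The case against.** The strongest reply is that the text, read literally, already does the right thing. Creatinine and eGFR are levels after transplantation, each follow-up time has an arm term, and so nothing is constrained. That reading is tenable and harmless. It is not stated, however: the single-group rule follows a list that begins with these markers and does not exempt them.

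A reader might infer that the model must either waste its adjustment or remove part of a real stent effect. The documents do not support that. No passage calls a post-operative value baseline, and pooling the arms at baseline makes sense only for a value taken before randomisation. Even in case 3, the loss depends on an early effect in the same direction as the later one. Section 5.1 gives both arms a 7 French stent with its tip in the renal pelvis, so the early difference could be near zero. An early difference that later vanished would instead produce a spurious later difference of opposite sign.

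A reader might also take section 8.1.3 ("donor age and gender, recipient age and gender, body mass index, smoking") as saying that donor characteristics predict graft function. It links them to the main study parameter, which is PCN placement. Their value here is an assumption, and using them is a matter of precision only.

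It is also fair that a SAP, not shown, may define the baseline, and that creatinine and eGFR are absent from the objectives in section 2 and the endpoints in section 8.1.2. Obstruction is captured more directly by PCN placement, stent obstruction and reintervention. These points limit the weight of the finding. They do not remove it, because the model itself is stated in section 10.2.

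**Conclusion.** The point holds as a minor one. Section 10.2 applies a common-baseline model to two markers that it defines only after transplantation. With a pre-operative baseline there is no bias, little precision to gain, and mild inflation of model-based tests: about 0.06 to 0.08 per time point under heteroskedastic compound symmetry. That size rests on assumed correlations of 0 to 0.2 with baseline and 0.5 to 0.7 among follow-ups, and on the absence of an unstructured option. With post-transplant values only there is no harm. Dilution of a stent effect is conditional on a choice that the protocol does not make, and should not be reported as a property of the plan. The primary Fisher test and the sample size are untouched.

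**What to change.** In section 10.2, limit the common-baseline term to the questionnaires. For creatinine and eGFR, state that only post-transplant values enter, with an arm term at every time point including the first, so that the joint test covers them all. Add donor age and gender, already collected under section 8.1.3, as prespecified covariates. If their correlation with the outcome is 0.3 to 0.5, this is worth about 10 to 33% more patients for this analysis; if it is near zero, little is gained.

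The cost is a few lines of text, with no new data and no change in sample size. The small downside is that these two markers get a slightly different model from the questionnaires. If the sponsor prefers to keep a baseline for them, the text should name a pre-randomisation value and allow an unstructured covariance.
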